## Abstract

Attention deficit hyperactivity disorder (ADHD) is a disorder characterized by hyperactivity, impulsivity and lack of attention. It can have a major impact on everyday life and result in negative consequences for one's personal, academic, and work situation. For individuals with symptoms of ADHD, increased levels of anxiety and depression are common, and an overall reduction of quality of life is often present. This study protocol describes a clinical trial of internet-based cognitive behavioral therapy (iCBT), using a randomized controlled study design, with the primary aim to increase quality of life, as well as to reduce symptoms of ADHD, anxiety, depression, and stress. A second aim is to investigate, by qualitative means, what aspects of treatment were perceived as helpful and hindering when it comes to completing iCBT. Two hundred participants with symptoms of ADHD will be included and randomized to two conditions (treatment and wait-list control). The treatment period is comprised of a maximum of ten weeks, with two mandatory modules and ten modules from which the participants can choose freely. Self-report measures will be completed by the participants at baseline and end of treatment, as well as at a six-month follow-up. The treatment is guided by therapists and consists of weekly correspondence with the participants. The study will utilize an intention to treat design, with ANOVAs and Reliable Change Index to evaluate treatment effects. The qualitative part of the project will be interview-based and employ thematic analysis. Lastly, a psychometric evaluation of a common instrument for determining ADHD-symptoms will also be made. The results will hopefully contribute to the evidence base for iCBT for individuals with symptoms of ADHD and help disseminate potentially effective interventions.

## Introduction

1

Attention deficit hyperactivity disorder (ADHD) is a condition that is characterized by symptoms of hyperactivity, impulsivity and lack of attention. The disorder can cause serious impairments for individuals in their everyday life and functioning (Kooij et al., 2010). The disorder is believed to be caused by genetic and neurological factors, with variance in symptom expression as a result of environmental factors (Barkley, 2015). Worldwide estimated adult prevalence is between two and 5 % (e.g., (Kessler and Adler, 2006; Simon et al., 2009). While national and international guidelines consistently advocate for the treatment of adult ADHD to be multidisciplinary (e.g., Kooij et al. (2019), in practice, pharmacotherapy may be the treatment of choice to aid attention and concentration (Dodson, 2005). Regardless of medication, individuals with ADHD-symptoms can still experience persistent impairment in certain contexts. One such environment is educational settings, particularly studying at a university (Gudjonsson et al., 2009). Most of the educational programs and courses offered in higher education require individuals to plan and execute curricular activities on their own and with little assistance from others, which is more difficult to manage if one is struggling with symptoms of ADHD. Studying at a university is also characterized by a large degree of freedom, distal deadlines, task aversiveness, and many distracting elements, which can cause procrastination and difficulties engaging in goal-directed behavior for most people in general (Svartdal et al., 2020), and individuals with ADHD-symptoms in particular (Niermann and Scheres, 2014). One way of overcoming the problems associated with ADHD-symptoms in educational settings is to provide some form of learning support, for instance tutoring and coaching. DuPaul et al. (2017) have demonstrated that such help can increase grade point averages. However, this type of assistance is specifically aimed towards curricular activities, while leaving such psychological complaints as anxiety and depression unaddressed.

Another environment in which individuals with ADHD-symptoms may experience difficulties is the working environment. Functioning at work can be impaired by ADHD symptoms in several ways, creating problems carrying out specific tasks, which in turn increases stress levels and affect interpersonal relationships (Polanczyk et al., 2007). Individuals with ADHD-symptoms often have difficulties with organization, prioritizing, and following through on instructions, which negatively impact performance at work (De Graaf et al., 2008). Furthermore, symptoms of ADHD have been found to be related to greater fatigue, burnout, and long-term sick-leave (Combs et al., 2015). Hence, providing support for individuals with symptoms of ADHD might be an effective way not only to prevent some of the difficulties often experienced in occupational settings, but also risk factors that might contribute to or exacerbate mental distress (Ek and Isaksson, 2013; Oscarsson et al., 2022).

In addition to pharmacotherapy, psychological treatments may prove beneficial in helping individuals with ADHD-symptoms manage problems in different contexts as well as co-existing psychological complaints (Lambez et al., 2020). However, few studies have examined the effects of psychological treatments for individuals ADHD-symptoms. A recent systematic review suggest that Cognitive Behavior Therapy (CBT) has strong empirical support, with positive effects on measures of both primary (symptoms) and secondary (psychosocial) adult ADHD outcomes, but that the number of studies are few and suffer from methodological issues (Fullen et al., 2020). Similarly, a meta-analysis also found positive effects of more behaviorally-oriented interventions often included in CBT, e.g., behavioral modification, but concluded that the number of publications is small and further research is warranted (Hodgson et al., 2014).

Ramsay (2010) has proposed a CBT-model adapted for adult ADHD, largely based on Barkley's (2015) model of ADHD as an executive function deficit disorder. Ramsay's model includes consideration of the executive dysfunction, as well as the developmental experiences of ADHD adults. This includes recognizing cognitions related to a history of perceived failures, and self-mistrust. With general consensus regarding required coping strategies and techniques for adults with ADHD (e.g., reducing distractions, using planners, behavioral activation), the main challenge for patients and their therapists is the implementation of these skills in everyday life (Ramsay, 2016).

Meanwhile, psychological treatments for ADHD-symptoms might not always be readily available. One way of overcoming this problem of outreach is to provide online interventions, which has proven to be an effective mean of disseminating aid for many psychiatric disorders (Andersson et al., 2019), but is less explored for ADHD-symptoms (Păsărelu et al., 2020). To date, only one meta-analysis has been carried out, which included six studies and found that internet-based interventions increased attention and social functioning. Still, despite some indications of benefit, the number of studies were few and included small sample sizes (*n*s < 30), highlighting the need for additional research (Shou et al., 2022). Apart from outcome studies, investigations on the feasibility and usability of online interventions and smartphone applications have also been made. Overall, this type of research indicate that such means of delivery are accepted and perceived as user-friendly (Knouse et al., 2022), but that issues of content and engagement are important to consider (Kenter et al., 2022; Nordby et al., 2021). A recent study that explored the feasibility of a proposed online intervention for ADHD-symptoms also demonstrated a high acceptability towards this type of aid, and that 59 % of the participants actually preferred online to face-to-face interventions (Shelton et al., 2022). With additional studies investigating online interventions for ADHD-symptoms under way (Kenter et al., 2021), the interest in developing and disseminating this type of support seem to be growing and could, if found to be effective, help more individuals with ADHD-symptoms deal with everyday life and functioning.

### Aims of the study

1.1

Given the scarcity of research on psychological treatments for ADHD-symptoms in general, and internet-based interventions in particular, there is a need for additional studies in order to test their efficacy. This is especially true for adequately powered randomized controlled trials with longer follow-up assessments (Shou et al., 2022). Furthermore, given the many challenges that face individuals with ADHD-symptoms in both educational and occupational settings and the lack of support being provided in these contexts, providing online interventions may prove to be helpful for many university students and employed individuals with these types of issues. Thus, the aim of the current study is to conduct a clinical trial examining the effects of an internet-based intervention for individuals with ADHD-symptoms to determine its impact on inattention, restlessness, psychological complaints, and quality of life among university students and individuals working at-least part time in Sweden. Results from a previous Swedish study that guided use of smartphone applications for individuals with ADHD-symptoms implies that online interventions can be accepted and generate benefits in terms of reduction of inattention (Moëll et al., 2015), but further research is needed. In addition, there is also a need to understand the experiences of undergoing such a treatment to find out what aspects of online interventions are most useful, and which might warrant further refinement. The following research questions will be addressed:

### Research questions

1.2

•What are the group-average outcomes of the online intervention at the end of treatment and at a six-month follow-up?•How many individuals experience a reliable change when it comes to ADHD-symptoms and quality of life at the end of treatment and at a six-month follow-up?•Did the participants experience any negative consequences in relation to the online intervention?•How do participants who have discontinued treatment view the online intervention and their participation?•How do people who have undergone the entire treatment (≥ six modules) perceive the online intervention and their participation, both in terms of helping and hindering aspects?•What are the psychometric properties of the Swedish translation of ASRS in a Swedish population?

## Material and methods

2

### Procedure

2.1

Participants will be recruited via two contexts; 1) educational settings, using student healthcare centres at different universities in Sweden, and information in emails, advertisements on campus, and social media aimed at university students, and 2) occupational settings, using advertisements on social media. Furthermore, relevant patient organisations will also be contacted and asked to inform their members about the study. In addition, a website where studies of online interventions are advertised will also help out with outreach (www.studie.nu). Those interested in participating will then sign up via a survey hosted at REDCap, i.e., a secure online platform for data collection (Harris et al., 2019), and submit baseline data, i.e., demographics and self-report measures. Informed consent by the participants will be submitted at this stage. Those individuals fulfilling the initial inclusion criteria will then be contacted by members from the research team in order to conduct a structured clinical interview to determine eligibility for inclusion and whether any exclusion criteria are fulfilled in terms of the presence of a severe mental disorder, i.e., the The Mini-International Neuropsychiatric Interview (MINI) (Sheehan et al., 1998). The participants will be allocated into two groups: treatment and control group. The participants in the treatment group will receive information about how to sign up to the treatment platform that is supplied by Psykologpartners W & W AB, a private healthcare provider in Sweden who have developed and manages the online intervention that is being tested in the current study. The participants will undergo a 10-week treatment program targeting common symptoms for individuals with ADHD. The treatment is guided by weekly check-ins by a therapist who receives weekly supervision, i.e., a psychologist in training undergoing basic clinical education in CBT at Uppsala University.

The participants will complete the same survey at the end of the online intervention, with the addition of the Negative Effects Questionnaire (NEQ; Rozental et al., 2019). Participants will also complete a similar survey at a six-month follow up, but this time without the NEQ (see Table 1 for an overview). After the six-month follow-up, the control group will be offered to receive the same online intervention as the treatment group, who in turn will complete the same surveys as described above. Participants in the control condition will respond to a self-report measure (PHQ-9) on depression weekly throughout their participation to monitor any eventual deterioration or suicidal ideation. If a participant receiving the online intervention decides to end treatment prematurely, the participant will be contacted to partake in an interview and asked to still complete the survey given at the end of the treatment period. Meanwhile, participants completing the full online intervention will be asked to partake in an interview about what they experienced as beneficial and hindering about the treatment. For the psychometric evaluation of the ASRS, data from the baseline screening will suffice to answer the research question. The recruitment will commence in February of 2023 and will end in September to October of 2023.

**Table 1 t0005:** Overview of the self-report measures.

Self-report measure	Assessment		
	Baseline	Post-treatment	Six-month follow-up
AAQoL	X	X	X
ASRS	X	X	X
GAD-7	X	X	X
PHQ-9	X	X	X
PSS	X	X	X
NEQ		X	

AAQoL = Adult Attention-deficit/hyperactivity disorder Quality-of-Life scale; ASRS = Adult ADHD Self-Report Scale-V1.1 (ASRS-V1.1) Symptoms Checklist; GAD-7 = Generalized Anxiety Disorder; PHQ-9 = Patient Health Questionnaire; PSS = Perceived Stress Scale; NEQ = Negative Effects Questionnaire.

### Participants

2.2

A power analysis was conducted using G*Power 3.1 to ascertain the number of participants needed to detect differences at post treatment and follow-up. The sample size calculation was based on three time points: pretreatment, post treatment, and at a six-month follow-up for both groups. The anticipated effect size of the treatment was set to Cohen's d 0.1 and the analysis used was a repeated measures ANOVA with Tukey's post hoc test. The randomization is carried out via www.random.org using space noise a randomization principle. The allocation will be into two groups: treatment and waitlist control group. No concealment procedure was used since the participants in the control group were informed that they would receive treatment at a later stage. The low effect was set based on the fact that this type of treatment has not been thoroughly researched and several existing studies have demonstrated a small effect. As a result, the number of participants needed was 138, but it was decided to include 200 participants to account for an expected high dropout rate. As for the qualitative studies, twelve to fifteen participants for each study will be interviewed, which is regarded as adequate to achieve code saturation in the qualitative analysis (Hennink et al., 2017). In terms of the psychometric evaluation of the ASRS (Study 5), two hundred participants are considered sufficient for determining internal consistency, convergent and divergent validity with other self-report measures, and to conduct exploratory and confirmatory factor analyses. See Fig. 1 for a flow chart over the recruitment process.

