### Inclusion and exclusion criteria

2.3

In the current study, the following inclusion criteria will be used when assessing whether an individual can get access to psychological treatment:1)Over 18 years old of age.2)Can read and write in Swedish.3)Have access to a computer, tablet, or smartphone with an Internet connection.4)Have previously been diagnosed with ADHD.5)Are studying at a university or college in Sweden or working at least 50 % of a full time-employment.

The following exclusion criteria will be used:1)Shows elevated symptoms of depression or risk of suicide, i.e., a total score on the Patient Health Questionnaire – 9 items ((PHQ-9; Kroenke et al. (2001), >15 points, or scores >2 points on question i) concerning suicidality.2)Has started or changed their medication for any psychiatric diagnosis in the last three months.3)Exhibits another form of psychiatric diagnosis that requires more specialized care, for example substance abuse syndrome, anorexia nervosa, bipolar disorder, psychotic symptoms, or schizophrenia, as assessed with the MINI (Sheehan et al., 1998). There are no additional exclusion criteria for the qualitative studies regarding dropouts or participants that completed the treatment.

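### The reason given for omitting allocation concealment is a blinding argument; concealment is feasible in this open waitlist trial and should be stated

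*Protocol article*

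**What the plan says.** Section 2.2 (Participants) names the source of the random numbers: "The randomization is carried out via www.random.org using space noise a randomization principle". It then describes the arms, "The allocation will be into two groups: treatment and waitlist control group", and continues: "No concealment procedure was used since the participants in the control group were informed that they would receive treatment at a later stage".

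Section 2.1 (Procedure) describes entry to the trial. Applicants "sign up via a survey hosted at REDCap, i.e., a secure online platform for data collection" and give demographics and self-report measures there. On consent it says "Informed consent by the participants will be submitted at this stage". Those who meet the initial criteria are then "contacted by members from the research team in order to conduct a structured clinical interview to determine eligibility for inclusion". Allocation is mentioned after this, in the passive, and no one is named as carrying it out. The control group is offered the intervention after the six-month follow-up.

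Section 2.3 (Inclusion and exclusion criteria) lists the rules that the interviewers apply. The third exclusion criterion begins "Exhibits another form of psychiatric diagnosis that requires more specialized care" and goes on to an open list of examples, assessed with the MINI.

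**The concern.** Concealment and blinding are separate safeguards. Concealment acts before assignment: whoever decides that a person enters the trial cannot know or change that person's arm until the decision is final. Blinding acts after assignment, on what participants, therapists or assessors know. A waitlist trial of a guided online treatment cannot blind its participants, but it can conceal its allocation. The article gives the impossibility of the second as its reason for not doing the first.

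What is at stake is the comparability of the arms at entry. If the arm can be known or altered while eligibility is still open, whether a borderline applicant is accepted, or whether a draw is accepted, can depend on the arm. Adjustment for measured baseline scores does not remove selection on prognosis that was not measured. A motive is easy to imagine without assuming bad faith, since a distressed applicant assigned to the control group waits until after the six-month follow-up.

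**Working it through.** No figure is in dispute, so the check sets the relevant statements side by side.

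1. **Is concealment merely unmentioned?** No. Section 2.2 says that none was used. The allowance that a journal article may leave detail to a fuller document does not cover a safeguard that the article itself reports as omitted.

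2. **Does the reason support the omission?** The premise is that controls knew they would be treated later. That is knowledge held by participants about their own arm after assignment. The conclusion is about a procedure that governs staff before assignment. The premise can be true while allocation is fully concealed, so the conclusion does not follow.

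3. **Who decides eligibility?** Members of the research team, by structured interview (section 2.1).

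4. **How much room for judgement is there?** Most criteria in section 2.3 are rules: age, language, internet access, a previous ADHD diagnosis, study or work status, PHQ-9 above 15 or the suicidality item above 2, and a medication start or change in the last three months. The third exclusion criterion is different. The MINI structures the diagnosis, but whether it calls for more specialised care, against an open list, is a judgement.

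5. **Who draws, when, and is the draw final?** Section 2.2 names only a website. Nothing states who uses it, whether the sequence is made in advance or one draw at a time, when the result is released, or that a draw may not be repeated.

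6. **Does the order of events protect the trial?** In part. Consent and baseline measures come at sign-up and the interview follows, with allocation described afterwards. Baseline self-reports therefore precede knowledge of the arm. But the article does not say that eligibility is recorded and closed before the arm is known.

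7. **Does the intention-to-treat analysis protect the trial?** In part. Section 2.8 (Statistical analysis) commits to that principle, which keeps people counted as randomised in their arm. It does not help if a draw is repeated, or if someone is declared ineligible after the draw and never counted.

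**Routes left open by steps 3 to 7:** the judgement-based eligibility decision, a redraw, and an exclusion after assignment.

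**Size.** If a share p of an arm entered because of the arm, and these people differ in prognosis by δ from those who would otherwise be there, the arm mean shifts by p × δ. The documents give neither p nor δ and nothing that bounds them, so no figure is offered.

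**The case against.** The strongest reply is that this is a slip of terminology. The stated reason makes sense only for blinding, so the authors may have meant that participants were not blinded. On that reading the defect is one wrong word plus silence about who holds the sequence, which a condensed article often leaves to the full protocol. The reading is plausible. It does not remove the point: the sentence would then misreport the trial by disclaiming a safeguard, and would still need correcting.

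It is also fair to say that the exposure is narrow. Consent and baseline data come first, most criteria are rules, and single draws made after eligibility is settled would be hard to predict. All of this stands. It limits the exposure to the routes listed in the working but does not close them.

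Some stronger readings are tempting, and the documents do not support them:

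- A reader might infer that the interviewers themselves make the draws. The article names no one; it only fails to state a separation.
- A reader might link the point to the open, self-reported outcomes. Those create performance and detection bias, which concealment does not cure.
- A reader might suppose that the survey platform makes the remedy free. The article describes REDCap only as a tool for data collection.

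**Conclusion.** The point holds in a limited form. Section 2.2 expressly omits allocation concealment and justifies this with an argument about blinding. The justification is invalid, and concealment remains feasible in this design. With eligibility decided by interview, one criterion open to judgement, no stated separation of roles and no statement that a draw is final, entry to the trial could depend on the arm.

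The conclusion that the stated reason fails needs no assumption. The conclusion that there is exposure rests on taking the word concealment as written, and on the article's silence about who draws and when an arm is released. A reader might go further and infer that selection bias occurred, or that it is large against the anticipated effect. The documents support neither. They show that a route is open, not that it was used, and the size cannot be derived from them.

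**What to change.** Replace the concealment sentence in section 2.2 with text along these lines:

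> Participants are not blinded to their group. The random.org sequence is held by a member of the team who does not conduct the eligibility interviews. Each assignment is released once, without redraw, only after consent, the baseline survey and the interview are complete and eligibility has been recorded.

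If some participants have already been randomised, apply this to the rest and report how the earlier ones were allocated. If the procedure was in fact concealed and only blinding was meant, correct the sentence to describe what was done.

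The cost is modest: the administrative work of separating the two roles within the existing team and keeping a record of when eligibility was settled. The remedy does not depend on any particular software, nor on a change to the method of generating the sequence.

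The change protects only participants not yet randomised, so it should be made while recruitment is open.

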#### Patient Health Questionnaire – 9 Items (PHQ-9)

2.5.4

The PHQ-9 is a nine-item instrument measuring depression. It has excellent internal consistency (Cronbach's α = 0.89) and a good test-retest correlation (*r* = 0.84; Kroenke et al., 2001). The instrument has a single-factor solution. The score ranges from 0 to 27 points (Kroenke et al., 2001). Items range from 0 (“Not at all”) to 3 (“Nearly every day”). One example of an item is: “Over the last 2 weeks, how often have you been bothered by any of the following problems? Little interest or pleasure in doing things.” (Item 1).

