### Statistical analysis

2.8

All outcomes will be analyzed using a series of ANOVAs, according to intent-to-treat-principle and missing values will be handled by using multiple imputation. Bonferroni-corrections to adjust for family-wise errors will also be used. The only exception applies to the NEQ which is only reported descriptively. Individual changes on the AAQoL and ASRS are determined using the Reliable Change Index (Jacobson and Truax, 1992; Maassen, 2004), i.e., yes/no, for improvement, deterioration, and non-response. For recovery, the Reliable Change Index and a positive change of two standard deviations in the direction of functionality will be used, i.e., criterion a (Jacobson and Truax, 1992). Given the large sample size that the study aims to recruit, moderation analyses are possible to conduct, but will be performed post hoc. Exploratory and confirmatory factor analyses will be used alongside reliability calculations (Omega) and analytic techniques used in Rasch analysis.

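### The sample size of 138 does not follow from Cohen's d 0.1 with three time points; it fits Cohen's f 0.1, so the stated sensitivity is wrong

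*Protocol article*

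**What the plan says.** The sample size is justified in section 2.2 (Participants) of the protocol article.

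- Software and purpose: "A power analysis was conducted using G*Power 3.1 to ascertain the number of participants needed to detect differences at post treatment and follow-up".
- Measurements: "The sample size calculation was based on three time points: pretreatment, post treatment, and at a six-month follow-up for both groups". Table 1 in section 2.1 also shows three assessments.
- Effect: "The anticipated effect size of the treatment was set to Cohen's d 0.1". The text defends this as a deliberately low value for a little-studied treatment.
- Test: "the analysis used was a repeated measures ANOVA with Tukey's post hoc test".
- Arms: "The allocation will be into two groups: treatment and waitlist control group".
- Result, presented as following from the above: "the number of participants needed was 138, but it was decided to include 200 participants to account for an expected high dropout rate".

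Alpha, power, the correlation between repeated measures, the ANOVA effect tested and the dropout rate are not given. Section 2.8 (Statistical analysis) adds that "Bonferroni-corrections to adjust for family-wise errors will also be used".

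**The concern.** A standardised difference of 0.1 is very small, and 138 people in two arms is far too few to detect it in ordinary circumstances. G*Power's repeated measures ANOVA takes its effect size as Cohen's f, and for two groups d = 2f. Entering 0.1 in that field and reporting it as d would therefore overstate what the trial can detect.

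The effect size is the only statement in the article of what difference the trial is sized to find. If its metric is wrong, readers will think the trial is sensitive to a much smaller effect than it is. The dropout margin is also affected, because it is the gap between the required number and 200.

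**Working it through.** **Inputs from section 2.2.** k = 2 groups, m = 3 measurements, d = 0.1, required N = 138, enrolled N = 200.

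**Assumed, because not stated.** Alpha 0.05, power 80%, r = 0.5, sphericity, equal arms, test of the group-by-time interaction. The value of r is varied below.

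**Formulas.** The power of the interaction test comes from the noncentral F distribution with

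- λ = f² × N × m / (1 − r)
- df1 = (k − 1)(m − 1), df2 = (N − k)(m − 1)
- f = d/2 for two groups, so d = 0.1 is f = 0.05.

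**Step 1: the plan's figure from its stated inputs.** With f = 0.05, m = 3 and r = 0.5, 80% power is first reached at N = 644: λ = 0.0025 × 644 × 3 / 0.5 = 9.66, df 2 and 1284, power 80.0%. At N = 138, λ = 0.0025 × 138 × 3 / 0.5 = 2.07 and power is 23%. So 138 is not reproduced. The interaction is a favourable choice: the between-groups test, with λ = f²Nm / (1 + (m − 1)r), would need 2,096.

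**Step 2: can the unstated r rescue it?** A higher r lowers the required N:

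| r | N for d = 0.1 (f = 0.05), m = 3 |
|---|---|
| 0.5 | 644 |
| 0.7 | 388 |
| 0.8 | 260 |
| 0.84 | 208 |
| about 0.89 | 138 |

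The only stability figures in the article are 0.84 for the PHQ-9, described as "a good test-retest correlation" in section 2.5.4, and 0.83 for the GAD-7 in section 2.5.3. Neither is a main outcome, and the value needed lies above both. At r = 0.84, power at 138 is 61% (λ = 0.0025 × 138 × 3 / 0.16 = 6.47).

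**Step 3: what does give 138?** Reading 0.1 as f, with alpha 0.05:

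- m = 4, r = 0.5, 80% power: N = 138 exactly (λ = 0.01 × 138 × 4 / 0.5 = 11.04, df 3 and 408, power 80.1%).
- m = 3, r = 0.5, 80% power: N = 164. Power at 138 is 73%.
- m = 3, r about 0.58, 80% power: N = 138.
- m = 3, r about 0.68, 90% power: N = 138.

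**Step 4: what f = 0.1 means between arms.** Suppose the arms are equal at baseline and differ by δ SD at both later visits. The arm difference is then (0, δ, δ), with mean 2δ/3. The interaction terms are ±(−δ/3, δ/6, δ/6), and their mean square is (1/9 + 1/36 + 1/36)δ²/3 = δ²/18. So f = δ/√18, and f = 0.1 gives δ = 0.1 × 4.243 = 0.42 SD. Under this pattern, a true difference of 0.1 SD would need 2,892 participants at r = 0.5.

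**Step 5: cross-check with a plain two-arm comparison at one visit.** n per arm = 2(1.960 + 0.842)²/d² = 15.70/0.01 = 1,570 for d = 0.1. Power for d = 0.1 is 8.5% with 69 per arm and 10.5% with 100 per arm. The difference detectable with 80% power is √(15.70/69) = 0.48 SD and √(15.70/100) = 0.40 SD respectively.

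**Step 6: dropout margin.** 1 − 138/200 = 31%. If 164 are needed, 1 − 164/200 = 18%.

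**The case against.** The strongest reply is that alpha, power and r are unstated, so nobody can say that 138 is wrong as a number. That stands. With f = 0.1 and three measurements, 138 is sufficient once r is about 0.58. A reader who sees the exact match at four measurements might infer that the wrong number of visits was entered. The article does not support that: it says three throughout, and three visits with a slightly higher r also yield 138. Nor can 164, 73% power or 18% tolerated loss be offered as the corrected values; each rests on an assumed r of 0.5 and an uncorrected alpha.

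A second reply is that a condensed article may leave alpha, power and r to a fuller document. That is fair, and their absence is not the point here. The point is that a stated metric and a stated result conflict.

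Third, the conversion to a between-arm difference depends on the assumed pattern: f = 0.1 is d = 0.2 by d = 2f, but 0.42 SD under the pattern in step 4. That is true, but neither value is 0.1, and using d = 2f in steps 1 and 2 favours the plan.

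Fourth, a reader might infer that the trial is too small, or that the authors would take a null result as excluding a small effect. The article says neither. With 200 and no loss, power for f = 0.1 is 88% at r = 0.5, three visits and alpha 0.05. Section 1.1 says only that adequately powered trials are needed, and the Discussion only that this sample is larger than earlier ones.

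**Conclusion.** The point holds for the effect-size metric. As written, d = 0.1 with two groups and three time points does not give 138. It gives 644 at r = 0.5 and 208 at r = 0.84, and reaches 138 only at r of about 0.89 (alpha 0.05, 80% power, sphericity, interaction test). The value 0.1 was apparently used as Cohen's f, but the document does not show which number of measurements and which r lay behind it.

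The stated sensitivity is therefore wrong. Under the equal-difference pattern, f = 0.1 is about 0.42 SD, roughly four times the stated 0.1. This does not show that 200 is too few for the effect apparently intended; whether 138 was enough depends on the r that was assumed.

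**What to change.** Revise the sample size paragraph in section 2.2:

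1. Replace the Cohen's d label with the metric actually entered, apparently Cohen's f 0.1 for the group-by-time interaction. Say what it means as a between-arm difference and under which pattern over time.
2. Rerun the calculation for three time points with the alpha, power and r actually assumed, and report them with the result. Restate either the required N or the power at 138. For f = 0.1, alpha 0.05 and 80% power, the required N is 196, 164, 130 and 98 at r = 0.4, 0.5, 0.6 and 0.7. If the Bonferroni correction in section 2.8 is meant to halve alpha across the two main outcomes, it is 194 at r = 0.5.
3. Restate the dropout that 200 tolerates so that it matches: for example, 18% if 164 are needed and 31% if 138.
4. Remove any implication that the trial is powered for d = 0.1.

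The cost is one rewritten paragraph and one rerun of the power calculation. Enrolment, design and analysis are unchanged. The stated sensitivity becomes less favourable, and the dropout margin may as well, depending on r.
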